**Aim 5: Test whether gamification of cognitive tasks influences participant experience and technology acceptance.**

Hypothesis: Compared to participants who complete standard, non-gamified cognitive tasks (e.g., NIH Toolbox), participants who complete equivalent, gamified cognitive tasks within Datacubed Health's app will report a more positive experience on a usability/Technology Acceptance Model (TAM) questionnaire. Delivering cognitive tasks in a gamified format on mobile device will increase standard TAM outcomes (e.g., perceived ease of use, perceived usefulness, attitude towards using, behavioral intention to use).

**Exploratory Aim 1: Test whether participant churn can be predicted from objective measures of participant engagement with the gamified smartphone app**

Hypothesis: Participant churn (i.e. dropout) will be predicted by measures of participant engagement with the gamified smartphone app. This analysis will be restricted to Arm A participants assigned to the gamified smartphone app condition. Churn will be defined as missing more than 25% of assigned instruments within a study phase (the 1 month, 3 month, and 6 month milestones). Potential markers of engagement will included the number of clicks on the avatar, number of changes made to the avatar, number of gem store purchases, and the total amount of time spent on the app.

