## **7) STUDY TIMELINES**

Each participant will be asked to complete surveys for six months after enrollment. Over the course of that six-month period, they will receive roughly one survey each week either by mail, within the smartphone app, through the Datacubed Health website, or through a third-party

website. Each survey will last no longer than 10 minutes, but most will be shorter (~3 minutes). A subset of participants who complete the initial six-month period will be given the option to continue into a two-week follow-up period, during which they will complete up to 6 more activities (cognitive tasks and usability/TAM surveys).

We plan to enroll all participants in the study within one year. We plan to complete primary analyses of the study data within two years.

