## 8) STUDY ENDPOINTS

The primary outcomes of interest are measures of *retention*, *compliance*, and *usability*.

- *Retention* will be defined as the amount of time participants remain active in the study. Specifically, the primary retention measure will be the number of days between the participant's first assigned study instrument and the date of the last assigned study instrument that they complete.
- *Compliance* will be defined as the number of instruments that the participant fully completes (i.e. responses for all required items) over the course of the study.
- *Usability* will be derived from a survey-based measure that assesses the perceived ease of use and pleasantness of the survey format (see separate attachment). The mean score across items of the survey measure will be used as the primary usability outcome measure of the overall usability of the survey format.

The exploratory outcome measures of interest are measures of *churn*, *engagement*, *activities*, and *routine*:

- *Churn* will be defined as missing more than 25% of assigned instruments within a study phase. Study phases will be defined at the 1 month, 3 month, and 6 month milestones.
- *Engagement* will be assessed based on participant behaviors while using the gamified mobile app (Arm A), and will include the number of clicks on the avatar, number of changes made to the avatar, number of gem store purchases, and the total amount of time spent on the app.
- *Activities* will be defined by classification of clusters of spatiotemporal geolocation data (Arm A).
- *Routine* will be defined by a directed graph model of the *activities*; characteristics will be explored using graph theoretic measures (Arm A).

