## 9) STUDY DESIGN AND PROCEDURES

### Arms A-D

This study will employ at initial recruitment a between-subjects design with four, independent arms, divided into two sequential cohorts.

Each participant will first complete the informed consent process (see Section 29). Upon receipt of the signed consent (signature captured digitally), Datacubed Health will assign the participant

to one of 4 groups; group assignment will determine the medium through which the surveys will be administered -- gamified mobile app (Arm A), web browser (Arm B & Arm D), or paper (Arm C). Approximately 100 participants are expected to be enrolled into each group.

Group assignment will be done sequentially by date and time of consent signature – i.e., the first participant who signs consent will be assigned to Arm A; the second participant, to Arm B; the third participant, to Arm C; the fourth participant, to Arm D; the fifth participant, to Arm A; the sixth participant, to Arm B; etc. The first cohort of participants recruited into each arm will receive compensation every two weeks based on how many instruments they complete (\$5/instrument). The second cohort of participants recruited into each arm will receive a single payment at the conclusion of the 6-month arm. Compensation will be the same, \$5/instrument, but delivered as a single lump sum payment after completion. The maximum, total compensation possible in the initial 6-month study period will be \$130.

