### **Exploratory Aim 1: Test whether participant churn can be predicted from objective measures of participant engagement with the gamified smartphone app**

An exploratory aim of the study is to identify objective measures of participant behavior on the gamified mobile app that predict retention, compliance, and engagement. Based on the behaviors of participants in the gamified mobile app group, we will use logistic regression and a random forest classifier to perform a survival analysis to predict participant “churn” (i.e. whether or not participants are retained at a given stage of the study). Churn will be predicted for the 3-month and 6-month milestones, based on participant behavior in the previous milestone (respectively at the 1-month and 3-month milestone). Features will include potential markers of engagement including the number of clicks on the avatar, number of changes made to the avatar, number of gem store purchases, and the total amount of time spent on the app. The importance of each feature will be explored to inform which features of the app most engage participants. The logistic regression and random forest classifier models will be compared based on their accuracy, precision, and the F1-score. A confusion matrix will be used to visualize the performance of the supervised learning algorithms; each row of the matrix represents the instances of the predicted class while each column represents the instances of the actual class. A range of thresholds (i.e. the probability threshold used to determine churn) will be explored to tune the accuracy and precision of the models.

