## **21) RESOURCES AVAILABLE**

Datacubed Health will provide the resources necessary to conduct this study, including the necessary infrastructure and financial support. (Subjects will use their own smartphones, pencils/pens, and computers, as applicable.) The organization will provide access to and support for the app. Datacubed Health will provide compensation to those participants as they are assigned to receive it. Participants will earn \$5 for each week of successful survey completion; participants can thus earn anywhere between \$0 (if no surveys completed at all) to \$130 (if surveys are successfully completed over 6 months, or 26 weeks). Payments will be processed and distributed to participants every other week, for the first cohort of 50 participants enrolled in Arms A, B, C, and D (approximately 200 participants). Payments will be processed after 6 months for the second cohort of 50 participants enrolled in each arm (approximately 200 participants). Participants who choose to enter the optional two-week follow-up period will receive one PayPal transfer consisting of \$5 for each survey or task completed in that time, after two weeks.

The study team, who will be based at the offices of Datacubed Health, is composed of multiple well-qualified full-time researchers who will devote the time necessary to conduct and complete the study. Members of the team include:

- [name] (PI), a PhD level behavioral neuroscientist with a master of public health and over 10 years of research and evaluation experience, including in clinical and population health, as well as survey design, implementation, and analysis.
- [name] (Research Scientist), a PhD level behavioral neuroscientist with XX years of research and clinical trial experience
- [name] (Associate Research Scientist), a BS level scientist with graduate-level coursework in biostatistics and epidemiology and 2 years of experience developing and testing methods for mobile data collection
- [name] (Assistant Research Scientist), a BS level scientist with three years of experience coordinating clinical research trials, including in digital health.

All members of the research team have been involved in the design of the study and will have access to the IRB-approved protocol. The PI will take primary responsibility for the conduct of the study and will delegate specific duties to other members of the study team as necessary.

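### Exploratory Aim 1 reduces a collected per-phase count of missed instruments to a yes/no churn label; modelling the count or the dates alongside that label is a cheap improvement

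*Protocol*

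**What the plan says.** Section 8 defines the outcome: "Churn* will be defined as missing more than 25% of assigned instruments within a study phase", with "Study phases will be defined at the 1 month, 3 month, and 6 month milestones". Section 2 (Objectives, Exploratory Aim 1) gives the same definition: "Churn will be defined as missing more than 25% of assigned instruments within a study phase (the 1 month, 3 month, and 6 month milestones". The aim is restricted to Arm A.

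Section 11 (Data analysis plan, Exploratory Aim 1) sets the method: "we will use logistic regression and a random forest classifier to perform a survival analysis to predict participant “churn". Churn is predicted at the 3-month and 6-month milestones from app behaviour at the preceding milestone. The features are avatar clicks and edits, gem-store purchases and time in the app. The two models are compared on accuracy, precision and F1 and shown in a confusion matrix. Then: "A range of thresholds (i.e. the probability threshold used to determine churn) will be explored to tune the accuracy and precision of the models".

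Section 9 says that the number of surveys completed and their completion dates are recorded for all participants. The same Section 11 paragraph opens by saying that the aim concerns behaviours that predict retention, compliance and engagement. Section 8 measures the first two in days and as a count.

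**The concern.** The outcome is available as a graded count with dates, but the plan uses only which side of 25% it falls on. No reason for 25% is given. Participants just below and just above the line are treated as different, while those on the same side are treated as alike however many surveys they missed. The survival-analysis label suggests that time to non-response is used; with a single status per milestone it is not.

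At stake is how well about 100 people can show which engagement markers go with later non-response, and how stable the resulting feature importances are. No primary or secondary result depends on it.

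**Working it through.** **1. Instruments per phase.** Inputs: "they will receive roughly one survey each week" (Section 7); "if surveys are successfully completed over 6 months, or 26 weeks", with a maximum of $130 at $5 each (Section 21). 130 / 5 = 26 surveys; 26 / 6 = 4.33 a month. Reading the phases as successive intervals:

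- month 1: 4.33, about 4 (used for predictors only; churn is not predicted there)
- months 1 to 3: 2 × 4.33 = 8.67, about 9
- months 3 to 6: 3 × 4.33 = 13

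Sections 4 and 29 speak of one to two surveys a week, so the counts could be larger. The argument does not depend on the exact number.

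**2. Where the cut falls.** Smallest whole number above 0.25m, that is floor(0.25m) + 1:

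- m = 9: 0.25 × 9 = 2.25, so 3 missed (33%)
- m = 13: 0.25 × 13 = 3.25, so 4 missed (31%)

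A scale of 0 to 9, or 0 to 13, becomes two categories.

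**3. Arm size.** "Approximately 100 participants are expected to be enrolled into each group" (Section 9), so about 100 in Arm A over both payment cohorts.

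**4. Information lost.** The protocol has no figure to reproduce here. Power of a two-sided 5% test for one standardised marker serves as a yardstick. All other inputs are assumptions: n = 100; mean miss rate 15 to 40%; within-person correlation 0.1 to 0.5; permanent dropout 0 to 90% of non-response; beta-binomial misses. Churn is analysed by logistic regression; the count by linear regression and by regression on its rank. The slope is set so that a count analysis has about 80% power.

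One set of scenarios (13 instruments, miss rate 25%, correlation 0.3, slope tuned to the linear count model):

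| Dropout share of non-response | Linear count | Rank of count | Churn cut | Loss vs linear | Loss vs rank |
|---|---|---|---|---|---|
| 0% | 76.9% | 81.3% | 64.0% | 12.9 | 17.3 |
| 30% | 81.9% | 88.8% | 76.1% | 5.8 | 12.7 |
| 60% | 82.1% | 93.4% | 80.8% | 1.3 | 12.6 |
| 90% | 84.7% | 93.9% | 85.6% | -0.9 | 8.3 |

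Range over all scenarios with 13 instruments, in points lost by the cut:

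| Dropout share | vs linear count | vs rank of count |
|---|---|---|
| 0% | 7 to 24 | 13 to 25 |
| 30% | -7 to 15 | 9 to 29 |
| 60% | -11 to 6 | 8 to 36 |
| 90% | -1 to 5 | 4 to 23 |

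With 9 instruments (fewer scenarios): -5 to 23 against linear, 6 to 32 against the better count analysis. Each scenario used 1,000 to 1,500 runs. The Monte Carlo standard error near 80% power is at most √(0.8 × 0.2 / 1000) = 1.3 points, so differences of one or two points mean nothing.

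**5. Other assumed models.** A simulation with logistic-normal misses and a weekly dropout hazard, comparing the correlation of the marker with the cut and with the count, gave gains for the count of 15.5 to 15.6 points (intermittent misses only), 5.5 to 9.1 (mixed) and about 0 (near-pure dropout). Both tests rejected about 5% under the null. A small run (600 trials) of logistic against robust binomial-count regression gave gains of 0.5 to 16 points. There the count test rejected 6 to 8% under the null, so part of that gain may be inflated type I error.

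**The case against.** **Power is not the aim's criterion.** Section 11 plans no significance test for this aim; it compares classifiers and explores feature importance. This stands. The power figures are only a gauge of information, and neither prediction accuracy nor the stability of the importances was simulated.

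**Churn is meant as a state.** Section 2 equates it with dropout and Section 11 with being retained or not, so a yes/no target is natural, and under near-pure dropout a linear count model gains nothing. This stands as a reason to keep the label. It does not make the label sufficient: four scattered misses out of 13 also count as churn, and Section 11 names retention and compliance among the things to be predicted.

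**The graded information survives elsewhere.** Compliance and retention are primary outcomes on their full scales. True, but over the whole study, not per phase in relation to earlier app behaviour.

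**Survival analysis may be loose wording.** Logistic models at successive milestones can be read as a coarse discrete-time approach. Even so, the point within a phase at which responses stop is not used.

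**Accuracy is not the only measure.** A reader might infer that the evaluation is empty because, if 30% churned, predicting that nobody churns would score 70% accuracy. The documents do not support that. Precision, F1 and the confusion matrix would expose such a rule, and the 30% in Section 3 is background on dropout in clinical trials, not a planning value. What remains is that all the listed measures depend on a threshold that is itself tuned.

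**Conclusion.** The point holds as a cheap improvement of low severity. The protocol itself fixes the binary outcome, so this is not a detail awaiting an analysis plan, and the discarded counts and dates are already collected.

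The size cannot be pinned down, because the protocol gives no miss rate, clustering, effect size or split between intermittent and permanent non-response. Where misses are purely intermittent, the cut lost power in every scenario: 7 to 24 points against a linear count model and 13 to 25 against a rank analysis. As dropout grows, the advantage of a linear count model shrinks to nothing and in some scenarios reverses, by up to 11 points. A rank analysis kept an advantage of 4 to 23 points even at 90% dropout.

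Three stronger readings are not supported:

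- A fixed loss, such as 5 to 16 points: results ran from below zero to about 36.
- A loss that disappears only when non-response is almost all dropout: with within-person correlation of 0.3 to 0.5 and a linear comparator, it is already under 5 points at 60% dropout, whereas against ranks it can persist at 90%.
- A 50% effective cut (2 of 4) in month 1 distorting the results: churn is not predicted for that phase.

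**What to change.** In Section 11, Exploratory Aim 1:

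- Add as an outcome the number of instruments missed out of those assigned in the phase. Use an ordinal model, or beta-binomial or quasi-binomial regression with robust or permutation inference. Permutation is the safer choice, given the 6 to 8% null rejection seen with a robust binomial model. Use a random forest in regression mode as the machine-learning counterpart.
- If the survival-analysis wording is kept, fit a weekly discrete-time model to the completion dates; otherwise drop the term.
- Report this alongside the 25% churn classification, which stays as the easily explained dropout label.
- Add an out-of-sample, threshold-free measure (AUC or Brier score) to accuracy, precision and F1.

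Cost: wording and slightly more analysis, with no new data or participants. The drawback is that a rate of missed instruments is less immediate to explain than churned or not churned.

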## 9) STUDY DESIGN AND PROCEDURES

### Arms A-D

This study will employ at initial recruitment a between-subjects design with four, independent arms, divided into two sequential cohorts.

Each participant will first complete the informed consent process (see Section 29). Upon receipt of the signed consent (signature captured digitally), Datacubed Health will assign the participant

to one of 4 groups; group assignment will determine the medium through which the surveys will be administered -- gamified mobile app (Arm A), web browser (Arm B & Arm D), or paper (Arm C). Approximately 100 participants are expected to be enrolled into each group.

Group assignment will be done sequentially by date and time of consent signature – i.e., the first participant who signs consent will be assigned to Arm A; the second participant, to Arm B; the third participant, to Arm C; the fourth participant, to Arm D; the fifth participant, to Arm A; the sixth participant, to Arm B; etc. The first cohort of participants recruited into each arm will receive compensation every two weeks based on how many instruments they complete (\$5/instrument). The second cohort of participants recruited into each arm will receive a single payment at the conclusion of the 6-month arm. Compensation will be the same, \$5/instrument, but delivered as a single lump sum payment after completion. The maximum, total compensation possible in the initial 6-month study period will be \$130.

Each participant will be informed immediately of their group assignment and compensation scheme. Participants who are assigned to the mobile app group will receive additional instructions on how to download and log into the app. Participants who are assigned to the Datacubed Health website group will receive an email with instructions and a link to log into the Datacubed Health web portal. Participants who are assigned to the third-party website (Qualtrics) will be informed that they should expect to receive an email with a custom link to complete surveys each week. The third-party website will not be provided with any participant information, including email addresses. Subjects will only be identified to the third-party website with unique, randomly generated alphanumeric IDs. A script hosted by Datacubed Health will link these IDs to participant email addresses, internally. A master list of alphanumeric subject IDs and participant email addresses will be visible only to study administrative staff at Datacubed Health. Participants who are assigned to the paper group will be informed that they should expect to start receiving their surveys by mail each week.

Participants in all groups will be assigned the same set of study instruments, in the same order. See separate attachments for a listing and full text of all planned survey instruments. Each instrument will take no more than 10 minutes to complete (including embedded instructions), but most will be substantially shorter (2-3 minutes).

Participants in the gamified mobile app condition must log into the mobile app and will see a rich user interface - this includes a customizable avatar, progress-tracking maps that are gradually revealed as study activities are completed, points earned by completing study activities that can be redeemed for virtual avatar accessories (e.g. a hat or sunglasses), and other appealingly designed features (e.g. animated confetti displayed when study activities are completed). Participants in the non-gamified web conditions (Datacubed Health and third-party) must log into the respective web platform and will simply see a scrollable list of available study activities. Participants in the paper condition will be mailed paper surveys, which they must return to the study team through mail using pre-addressed and stamped envelopes. Screenshots illustrating examples of each study condition are provided as a separate attachment.

After 6 months, participants who indicate that they wish to continue with the study will enter an optional two-week, follow-up period. Participants will be randomized to complete activities (cognitive tasks and usability/TAM questionnaires) in the same smartphone app used for the initial 6-month, study period, or using a secure email link. Participants will complete validated, commonly used cognitive tasks assessing working memory and decision-making (e.g., Stroop Task, Wisconsin Card Sort Task, N-Back task, etc.). After completing each cognitive task, participants will complete a brief usability/TAM questionnaire asking about their experience completing the relevant task. Participants in the app group will complete the usability/TAM questionnaire in the app, while participants in the web group will receive a separate secure email link to complete the same questionnaire.

Participants will receive \$5 for each week of the study if the study surveys for that week are completed. For the first cohort of 50 participants in each arm, reimbursements will be processed on a regular schedule (every other week) using PayPal, a third-party electronic payment system. For the second cohort of 50 participants in each arm, reimbursements will be processed once, after 6 months of participants. Participants who complete the optional two-week follow-up will receive \$5 via PayPal for each activity completed, after two-weeks. Participants will need to set up a PayPal account. This will require providing certain PII such as name, email address, and checking account information to PayPal and agreeing to the PayPal's privacy and security policies. DataCubed Health will require minimal PII (name and email address) to send payment to the participants through PayPal. These PII will be handled as described immediately below.

Certain personal identifiable information (PII), such as name, email address, and phone number, will be collected from all participants; mailing addresses will also be collected for participants in the paper group. These data will be used for administrative purposes only (e.g. contacting participants and sending surveys). For security, these data will be encrypted and stored in separate files, which can only be referenced through the anonymous subject ID that is assigned to each participant for the study. These data will be destroyed at the end of the study.

Certain demographic data, such as age (month and year of birth only; all subjects are under 90), gender, sex, ethnicity, education level, employment status, annual income level, and type of smartphone, will be collected from all participants. These data will be analyzed to see if they are associated with any differences in retention, compliance, and engagement. For security, these data will be encrypted and stored in separate files, which can only be referenced through the anonymous subject ID that is assigned to each participant for the study.

Survey data, including survey responses, number of surveys completed, and dates of survey completed will be collected for all participants. These data will be used to evaluate the study endpoints of participant retention, compliance, and usability.

In addition to the aforementioned data types, for the group assigned to the gamified mobile app, several types of data provided by the phone operating system will be collected:

- **Passive data:** These types of data will be collected even when the participant is not actively using the app. Specifically, the app will record information about the participant's

phone battery percentage, geolocation, number of steps taken, apps installed on the phone, and phone screen on/off times. Participants will be fully informed during the consent process that the app will collect such data. They will be able to disable collection of location and step count data at any time by restricting the app permissions via the phone operating system; Android phone owners will also be able to restrict permissions for data collection on screen time.

- Geolocation is the collection of precise geographical location (latitude and longitude) of a device through a mixture of GPS and WiFi signals. This technology is used by many other apps that provide services based on a user's location, such as navigation, rideshare, banking, dating, and fitness apps. When location permissions are allowed, location data is sent to the app every few minutes. In this study, geolocation data will only be used to develop a data-driven model of participants' daily routines. This model will then be compared with self-reported measures of daily activity to see if geolocation data can serve as a measure of activity and routine. Datacubed Health will not share geolocation data with any other external parties and will destroy this data at the end of the study.
- Once the data collection phase of the study is complete, participants will be automatically logged out from the app and all forms of passive data collection will cease. Additionally, most phone operating systems will not share geolocation data when the phone is in battery save mode and after the app has not been used by the user for a set period of time (length determined by the operating system).
- App behavior data: When a participant is using the app, data on the participant's behaviors within the app (e.g. which buttons are clicked, how frequently buttons are clicked, how long participants spend on certain screens, etc) will be collected.
- These passive data and app behavior data will be used to develop novel objective measures of participant behavior.

